### Data-analysis

We will compare the number of all biopsies and surgical procedures within one year after the first LCNB between the MRI group and the control group. To compare the diagnostic performance of MRI (in combination with mammography and ultrasound) and LCNB, a two-by-two table will be constructed in which the results of breast MRI in addition to mammography and ultrasound will be compared to the results of the histology of the tissue sampled at the large core needle biopsy. The positive predictive value will be calculated by dividing the number of correctly identified positives by the total number of positive Breast MRI's. The negative predictive value will be calculated by dividing dividing the number of correctly identified negatives by the total number of negative MRI's. Analyses will be performed for specific subgroups, i.e. microcalcifications and dense breast lesions on mammography. If the positive predictive value of mammography, ultrasound and Breast MRI is sufficiently close the positive predictive value of large core needle biopsy in patients with nonpalpable breast lesions in all patients or in a subgroup of patients, the biopsy in these patients may be replaced by MRI in the future. However, whether MRI can indeed replace LCNB in clinical practice will have to be assessed in a separate study.

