### Surgery

Depending on the size of the tumor, the size of the breast and patient preferences, the lesion will be removed following the institutions' guidelines for breast cancer management. MR images will be shown to and discussed with the surgeon before the operation. The number and type of surgical procedures (lumpectomy, re-excision, mastectomy, sentinel node biopsy or axillary lymph node dissection) will be reported until 1 year after the LCNB.

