## Statistical considerations

### Sample size

The statistical power of the study was calculated for the primary endpoint (reduction in the number of surgical procedures). Based on data of previous studies on nonpalpable suspicious breast lesions and literature, we expect 23% of patients with suspicious nonpalpable breast lesions to require more than one surgical procedure to remove all tumorous tissue [19,22-26]. This number includes patients with mammographically occult multifocal and multicentric disease (8%), patients who require a surgical re-excision because all tumorous tissue could not be removed in one procedure (10%) and patients with a DCIS lesion with a mammographically occult invasive component in the surgical specimen (5%) [19,22-26]. We expect that additional contrast enhanced Breast MRI will reduce this number to 11% due to earlier detection of invasiveness, multifocality and muticentricity and a better 3D depiction of the tumor. With a statistical power of 90% to detect this 12% reduction as significant (p < 0.05, two-sided), we will require 250 women in the control group and 250 women in the MRI group (95% confidence interval 6% to 19%). We consider a reduction larger than 5% clinically relevant.

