## Discussion

The purpose of the MONET – study is to evaluate whether performing contrast-enhanced Breast MRI in addition to mammography and/or ultrasound in patients with nonpalpable suspicious breast lesions will improve breast cancer management, i.e. to reduce the number of surgical procedures and/or the number of large core needle biopsies.

Many well conducted large clinical studies have been performed on the diagnostic performance of Breast MRI [5,6]. Only very few studies assessed the impact of Breast MRI on patient management. Two large observational studies have been performed to assess the value of Breast MRI for preoperative staging of patients with breast cancer [22,27]. The underlying assumption of both studies is that preoperative staging of the breast with MRI leads to the detection of mammographically occult multifocal and multicentric breast cancer, and that by removing these additional malignant lesions, the breast cancer recurrence rate could be reduced. Fischer et al compared the recurrent cancer rate in patients who did and did not undergo preoperative staging of the breast with MRI [22]. The reported recurrent cancer rate was indeed lower in the MRI group (1.2% (1/86)) than in the non-MRI group (6.5% (9/138)) after a mean follow-up time of 41 months. The percentage of contralateral tumors was lower in the MRI group as well: 1.7% (2/121) versus 4.0% (9/225). These differences were found to be statistically significant (p < 0.05) [22]. The recurrent cancer rate will also be assessed in the MONET – study: 5 years after completion of the MONET – study, the difference in recurrent cancer rate between patients from the MRI group and the control group will be assessed. Another study evaluated the change in surgical treatment after preoperative staging with MRI in patients with breast cancer [27]. Of the 267 patients that were scheduled for breast conserving therapy, the surgical plan of 69 patients (26%) was altered to more extensive surgery based on information obtained from preoperative staging with MRI. In 44 of these patients (64%) the alteration was considered to be appropriate based on pathological verification of malignancy in the surgical specimens [27]. Both authors advise preoperative staging with contrast-enhanced MRI in patients with breast cancer [22,27].

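### The primary procedure count ignores extent of surgery, so a fall achieved by larger first operations would be read as better management; plan a mastectomy comparison beside it

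*Protocol article*

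**What the plan says.** The Primary outcome section sets out to judge whether MRI improves management, and does so by the number of biopsies and operations in each arm over one year. Data-analysis repeats this: "We will compare the number of all biopsies and surgical procedures within one year after the first LCNB". The Discussion spells out better management as fewer operations and/or fewer core biopsies.

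The Sample size section uses a related proportion: "we expect 23% of patients with suspicious nonpalpable breast lesions to require more than one surgical procedure to remove all tumorous tissue". For the MRI arm it says "We expect that additional contrast enhanced Breast MRI will reduce this number to 11"%.

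On how MRI can change the operation, the Surgery section says "MR images will be shown to and discussed with the surgeon before the operation". The same section states that type of operation, mastectomy included, will be reported along with number. The Background lists conversion from lumpectomy to mastectomy among the repeat operations.

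The Discussion also cites a staging study in 267 patients scheduled for breast conservation: "the surgical plan of 69 patients (26%) was altered to more extensive surgery based on information obtained from preoperative staging with MRI". It adds: "In 44 of these patients (64%) the alteration was considered to be appropriate".

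**The concern.** Two women who each have one operation score the same, whether that operation was a lumpectomy or a mastectomy. A woman who has a lumpectomy and then a re-excision scores worse than one who has a mastectomy at once. Only the MRI arm has images that can move the surgeon towards a larger first operation.

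A lower count in that arm could therefore reflect better staging, more tissue removed at the first operation, or both. The primary comparison cannot tell these apart, yet the protocol would describe each of them as improved management. The trial's main conclusion is what is at stake; the validity of the count as a count is not.

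**Working it through.** **1. The plan's own figure.** Inputs from the Sample size section: 23% against 11%, two-sided 0.05, 90% power, 250 per arm. With pooled variance under the null and mean proportion 0.17:

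n = [1.960·√(2·0.17·0.83) + 1.282·√(0.23·0.77 + 0.11·0.89)]² / 0.12² = 204 per arm (221 with continuity correction).

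At 250 per arm the power is 94.9%. The 95% interval for the 12-point difference is 12 ± 1.96·√(0.1771/250 + 0.0979/250), or 5.5 to 18.5 points, close to the printed 6% to 19%. The stated size is larger than 90% power needs. That is conservative and does not bear on this point.

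**2. What the count does with a larger first operation.**

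| Course without MRI information | Course with MRI | Change in operations | Change in share with more than one operation |
|---|---|---|---|
| Lumpectomy, then re-excision or mastectomy (2) | Mastectomy or wider excision first, nothing further (1) | −1 | counts in favour of MRI |
| One sufficient lumpectomy (1) | Mastectomy first (1) | 0 | none |
| No extra biopsy | Biopsy of a lesion seen only on MRI | 0 (biopsies +1) | none |

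The first row is a gain for MRI. The second carries neither gain nor penalty. The third counts against MRI, but for sampling, not for excision.

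**3. Is the route plausible?** From the study cited in the Discussion:

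- plans enlarged: 69/267 = 25.8%
- judged appropriate: 44/69 = 63.8%
- remainder, by subtraction: 25/69 = 36.2%, or 25/267 = 9.4% of all patients. The article does not describe these 25 further.

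**4. Scale in this trial, as an illustration only.** Assume that 35.4% of 250 MRI-arm women have cancer (Preliminary results: 40 of 113 biopsy diagnoses, so not strictly a share of women) and that the cited rates carry over.

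- women with cancer: 0.354 × 250 = 88.5
- enlarged plans: 88.5 × 69/267 = 22.9, or 9.1% of 250
- of these, not judged appropriate: 88.5 × 25/267 = 8.3, or 3.3% of 250

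For comparison, with 58/250 control women having more than one operation, 40/250 in the MRI arm is the largest number that reaches significance: difference 18/250 = 7.2 points, pooled z = 2.03. How many of the roughly 23 enlarged operations would have averted a second one is not known.

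**5. Share of the expected effect.** Let f be the fraction of the 12 points that arises from larger first operations. The document gives no value, so the whole range is shown. The remainder is 12 × (1 − f) points.

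| f | Remainder (points) | Power for the remainder, 250 per arm |
|---|---|---|
| 0 | 12 | 94.9% |
| 0.25 | 9 | 73.8% |
| 0.50 | 6 | 38.8% |
| 0.67 | 4 | 19.4% |
| 1 | 0 | – |

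The remainder falls below the 5 points that the protocol calls clinically relevant once f exceeds (12 − 5)/12 = 58%. This is not an estimate of f. Nor is the part that f describes all over-treatment: a larger first operation for proven additional disease is what the trial hopes for. The table shows only that the reading of a positive result depends on a quantity that the primary comparison does not reveal.

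**The case against.** The endpoint is legitimate and several safeguards exist. Biopsies are counted as well as operations, including those for lesions seen only on MRI, which works against the MRI arm. Type of operation will be reported, so a shift to mastectomy would be visible. Recurrence will be compared five years after completion. The LCNB section sends additional MRI lesions that need sampling to second-look ultrasound or MRI-guided biopsy, so histology is sought before surgery is extended to them. Detailed comparisons by type of surgery are also something an article may leave to the full protocol or analysis plan.

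Much of this stands. It rules out three stronger readings that a reader might infer:

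- *MRI is credited every time lumpectomy becomes mastectomy.* It is not. The count falls only if a second operation is averted; an unneeded mastectomy is neutral.
- *Only operations are counted and extent is ignored altogether.* Biopsies are counted, and type of surgery is recorded and reported.
- *The over-treatment part of the effect can be computed by applying the 23% re-operation risk to the 9.4% whose change was not judged appropriate.* This assumes that those patients carry the average risk and that the wider operation removes all of it. They may be the patients least likely to have been spared a second operation, so the contribution could be near zero. The Discussion also says that the cited studies mixed palpable and nonpalpable tumours, while this trial enrols nonpalpable lesions only.

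The objection does not meet the remaining point. The article itself states the primary outcome, its comparison and its interpretation, and in none of these does extent of surgery enter. Reporting types of operation is not tied to the conclusion. Recurrence does not measure over-treatment. Biopsy of additional lesions does not cover a wider excision of the index lesion. The LCNB section says management is the same in both arms, but the Surgery section leaves the operation to tumour and breast size, patient preference and local guidelines, with MR images available in one arm only.

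**Conclusion.** The point holds in a limited form. The protocol equates a lower procedure count with better management, and the count can fall because a larger first operation replaced two smaller ones. A larger operation that was not needed leaves no trace in it. The cited study makes the route plausible: 25.8% of plans were enlarged, and 63.8% of those changes were judged appropriate. The share of the 12-point reduction that could arise this way cannot be fixed from the document; it may lie anywhere from none to all. The illustration of about 23 enlarged operations in the MRI arm rests on the 35.4% malignancy figure and on rates from a different mix of patients, and should not be quoted as a forecast.

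This is a weakness in what the endpoint is taken to mean. It is not an arithmetic error or a contradiction, and the primary endpoint need not be replaced. It ranks as a cheap improvement.

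**What to change.** In Primary outcome and Data-analysis, add a planned between-arm comparison, among all randomised women, of (a) mastectomy as first operation and (b) mastectomy as final operation within one year. Give each as a difference in proportions with a 95% confidence interval, and report both beside the primary result. All randomised women should be the denominator so that the comparison matches the primary one.

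Add a sentence on interpretation, for example: *A lower number of procedures will be described as improved management only together with the comparison of mastectomy between the arms.*

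A comparison of wider surgery without malignancy in the additional tissue should not be promised as things stand. It needs a surgical plan made before the MRI, and the pathology of the additional tissue. The article lists neither, and MRI comes before the core biopsy. It could be added only if both are recorded.

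Cost: one more planned comparison from procedure types that the Surgery section already records, with no change to endpoint, sample size or care. No power is claimed for it, so it should be read by its interval. The downside is that it may temper a favourable primary result.

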## Background

Breast cancer is the most frequently occurring malignant disease in women with a lifetime risk of 1 in every 8 – 9 women [1]. Like many other Western countries, the Netherlands launched a screening program for breast cancer and since 1998, all women between 50 and 75 years of age are offered biannual mammographic examination. This program reveals approximately 4000 suspicious, nonpalpable breast lesions each year in the Netherlands [2]. In clinical practice, another 3000 nonpalpable lesions are detected annually in women with a high genetic risk or a history of breast cancer [3]. Of all suspicious nonpalpable breast lesions, 10–55% of lesions turn out to be malignant (ductal carcinoma in situ or invasive carcinoma) after large core needle biopsy (LCNB) depending on the aggressiveness of the referral of patients which varies across countries [4]. Subsequently, these patients are scheduled for surgical removal of the malignant breast tumor. In a relatively high proportion of these patients (approximately 20–30%), several surgical procedures (re-excisions or conversions from lumpectomy towards mastectomy) are needed to achieve complete removal of the primary tumor. The reasons for this include unanticipated invasiveness, multifocality, axillary lymph node involvement or incomplete removal of the primary tumor [5]. A more accurate preoperative diagnosis could help to reduce the number of surgical procedures and invasive biopsies.

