### Study design

The MONET – study is a randomized controlled trial. Patients will be recruited in 3 hospitals: two large community teaching hospitals and one University Medical Center. In all participating centers, Breast MRI is not part of routine clinical practice in the work-up of patients with suspicious nonpalpable breast lesions. We aim to include a total of 500 patients with nonpalpable, mammographically suspicious breast lesions who are referred for biopsy. After giving informed consent, patients will be randomized in the control group or the MRI group. Patients in the control group (n = 250) will undergo routine medical care. This includes mammography, ultrasound, and the lesion is sampled by means of large core needle biopsy. In case of malignancy (DCIS or invasive carcinoma), the lesion is surgically removed. The MRI group (n = 250) will undergo routine clinical care and in addition, contrast enhanced Breast MRI in the University Medical Center prior to the large core needle biopsy. The MRI scan will be performed within one week after mammography and before LCNB which will be performed within one week after MRI to avoid a diagnostic delay.

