### Secondary outcome

Previous studies have shown that the positive predictive value of nonpalpable, BI-RADS 5 lesions detected on mammography is 96% [21]. If these lesions are classified as BI-RADS-MRI 5 as well, we expect the positive predictive value to increase further. In the 250 women who will undergo Breast MRI (intervention group), the positive and negative predictive values of Breast MRI in combination with mammography and ultrasound will be determined. If the predictive values are high (in certain subgroups, e.g patients with microcalcifications and dense breast lesions on mammography), LCNB could be omitted in the future in some women. Since all patients in the MONET – study will undergo LCNB, following clinical practice, the number of patients in whom LCNB could possibly be omitted in the future will be estimated based on the calculated predictive values of the MRI.

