## Preliminary results

Between January 2006 and November 2006, 174 patients were eligible for the MONET – study. 108 patients were included in the study (recruitment rate 62%). The reasons for non-participation are listed in Table 1. Eight patients were excluded after randomization (no available histology (n = 5), unanticipated obesity (n = 1), technical failure of MR scanner (n = 1), age over 75 years (n = 1)). Three of the excluded patients were randomized in the control group and 5 in the MRI group. The characteristics of the 100 patients included so far in the MONET – study are summarized in Table 2. The mean age was 56.1 years (range 39.9 – 75.0 years). In these patients, a total of 109 lesions were detected: 108 lesions were detected on mammography and 1 lesion on ultrasound imaging. The majority of the lesions were microcalcifications and classified as BI-RADS 3 or 4. The histological diagnosis of the lesions included 2 non-representative, 9 normal breast tissue, 62 benign lesions, 21 non-invasive carcinomas and 19 invasive carcinomas. So, 35.4% of lesions turned out to be malignant (non-invasive and invasive) after LCNB. Forty-five patients were randomized into the MRI group and 55 into the control group.

**Table 1 T1:** Reasons for non-participation

**Reason non-participation**	**Number of patients (%)**
Unable to lie in prone position	1 (1.5%)
Metal implants	6 (9.0%)
Severe obesity	1 (1.5%)
Claustrophobia	16 (24.0%)
Geographical distance from teaching hospital to MRI too long	18 (27.0%)
Clinical indication for MRI of the breast	1 (1.5%)
Personal reasons	23 (35.0%)
**Total**	**66**

**Table 2 T2:** Characteristics of the first 100 patients included in the MONET – study

n	**100**
Referred from University Medical Center	**30**
Mean age (*range*)	**56.1 **(*39.9 – 75.0*)
Number of lesions detected on mammography	**108**
*density only*	*41*
*microcalcifications only*	*54*
*both*	*9*
*other*	*2*
*unknown*	*2*
BI-RADS classification mammography	
*3*	*45*
*4*	*47*
*5*	*11*
*unknown*	*5*
Number of lesions detected on ultrasound (*mammographically occult lesions*)	**1**
BI-RADS classification ultrasound	
*3*	*1*
*4*	*-*
*5*	*-*
*unknown*	*-*
Diagnosis LCNB	**113***
*non-representative*	*2 (1.7%)*
*normal breast tissue*	*9 (8.0%)*
*benign*	*62 (54.9%)*
*non-invasive carcinoma*	*21 (18.6%)*
*invasive carcinoma*	*19 (16.8%)*

* 4 lesions were sampled twice because of inconclusive results

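### A single PPV from a two-by-two table covers only part of what LCNB delivers, so the count of biopsies that might be omitted after positive imaging could be too high

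*Protocol article*

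**What the plan says.** All places are in the protocol article.

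- **Data-analysis:** "a two-by-two table will be constructed in which the results of breast MRI in addition to mammography and ultrasound" are compared with the histology of the LCNB sample. The PPV is obtained by "dividing the number of correctly identified positives by the total number of positive Breast MRI's", and the NPV in the same way from the negatives. The section does not say which histology classes count as positive. It adds that biopsy may in future give way to MRI where the PPV of imaging comes near enough to that of LCNB, and leaves the actual decision on replacement to another study.
- **Secondary outcome:** here one reads "number of patients in whom LCNB could possibly be omitted in the future will be estimated based on the calculated predictive values", meaning those obtained for MRI.
- **Meaning of malignancy:** Study design has "In case of malignancy (DCIS or invasive carcinoma), the lesion is surgically removed", and Preliminary results has "35.4% of lesions turned out to be malignant (non-invasive and invasive) after LCNB". Both pool the two types.
- **LCNB:** histology gives the definitive diagnosis and is the basis for planning management. In-situ and invasive carcinoma are named as separate classes, with axillary staging as appropriate.
- **Abstract and Background:** the aim is to find a subgroup in which mammography, ultrasound and MRI together give a definite diagnosis.

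**The concern.** The question put to the secondary analysis is whether imaging could stand in for LCNB in some women. By the protocol's own description, LCNB supplies two things: whether the lesion is malignant and, if so, whether it is in situ or invasive. A two-by-two table tests agreement on the first only. A lesion can be a correct positive in that table while nothing has been shown about its type.

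The protocol treats type as relevant. Background, on why several operations may be needed, states: "The reasons for this include unanticipated invasiveness, multifocality, axillary lymph node involvement or incomplete removal of the primary tumor". It also names the detection of invasive components within DCIS as one of the added values of MRI. The secondary analysis as described cannot examine that value, although the histology needed is already recorded.

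At stake is the reading of one output of this trial, the number of women in whom LCNB might be omitted. If it is read as the number for whom positive imaging supplies what LCNB would have supplied, it could be too high.

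**Working it through.** **Step 1. Reproduce the plan's own figure.** Table 2 lists the LCNB diagnoses: 2 non-representative, 9 normal, 62 benign, 21 non-invasive and 19 invasive.
- Total: 2 + 9 + 62 + 21 + 19 = 113.
- Malignant: 21 + 19 = 40, and 40/113 = 35.4%. This matches the stated percentage.
- The base is LCNB results, since 40/109 lesions would be 36.7%.

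The protocol's own malignancy rate is therefore a pooled one.

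**Step 2. Split the pooled class.** From "21 non-invasive carcinomas and 19 invasive carcinomas", with exact Clopper-Pearson intervals:
- non-invasive: 21/40 = 52.5% (95% CI 36.1% to 68.5%)
- invasive: 19/40 = 47.5% (95% CI 31.5% to 63.9%)

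These are LCNB results from both arms, and four lesions were sampled twice. They are not a count of women, and the intervals treat the 40 results as independent.

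**Step 3. What the pooled PPV says about type.** Let s be the invasive share among the true positives. Then

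PPV(invasive) = PPV(any malignancy) × s.

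The two-by-two table records PPV(any malignancy) but not s. To show how little the first restricts the second, hold PPV(any malignancy) at 96%, the value that Secondary outcome cites for mammographic BI-RADS 5 lesions. Let s run from 20% to 80%; this range is an assumption with no source in the documents.
- s = 20%: 0.96 × 0.20 = 19.2%
- s = 80%: 0.96 × 0.80 = 76.8%

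Both cases give the same table and the same PPV. This illustrates the identity and does not estimate what the trial will find.

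**Step 4. Does another cut-off help?** If only invasive carcinoma counted as positive, in-situ lesions with positive imaging would become false positives, mixed with benign ones. No single binary split separates three classes (not malignant, in situ, invasive). The point therefore does not depend on how the missing definition of a positive is filled in.

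**Step 5. Set the sections side by side.**
- Aim (Abstract, Background): a definite diagnosis by imaging.
- What LCNB delivers (LCNB section): the definitive diagnosis, in classes that separate in-situ from invasive.
- Measure (Data-analysis): one PPV and one NPV.
- Output (Secondary outcome): a count of omittable LCNBs from those two values alone.

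The measure is narrower than the aim, and the output carries no qualification for the difference.

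**The case against.** **The pooling is inferred.** This stands as far as Data-analysis goes. Study design and Preliminary results make pooling the natural reading, and Step 4 shows that any other cut-off has the same limit.

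**The protocol does not claim that a high PPV settles the matter.** This stands. It speaks of a possibility, every trial patient has LCNB, and replacement is deferred to a separate study. A reader might infer that the plan would recommend omission; it does not. The count is nevertheless an output of this trial.

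**Omitting LCNB would not be shown to cause second operations.** A reader might infer that it would, because Sample size assigns 5 of the 23 percentage points to DCIS with an invasive part. That is a misreading. The invasion there is found in the surgical specimen, under routine care that already includes LCNB. Moreover, the LCNB section gives in-situ and invasive lesions one excision route, and only the word appropriate, applied to axillary staging, could separate them. The documents do not say how surgery differs by type, and they do not show the primary and secondary objectives pulling against each other.

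**A tempting figure is not supported.** Multiplying 96% by 47.5% gives about 46% as a PPV for invasive carcinoma. The 96% belongs to mammographic BI-RADS 5 lesions and the 47.5% to all lesions, of which only 11 of 108 were BI-RADS 5. A positive MRI on the scale described means suspicious for malignancy and does not promise invasion.

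**A tumour-type threshold for imaging cannot simply be added.** This stands: the suspicion scale in Interpretation of Breast MRI does not grade invasiveness, so such a criterion would be undefined.

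**The NPV is untouched.** Agreed. The point concerns omission after positive imaging only.

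**Conclusion.** The point holds as a limit on what the secondary analysis can show. A PPV for any malignancy covers only part of what the protocol says LCNB delivers. A count of omittable biopsies based on it could therefore be too high among women with positive imaging.

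The split is close to even in the available data: 52.5% of malignant LCNB results non-invasive, with a 95% CI of 36% to 69%. The pooled PPV thus says little about type, if positive imaging has a mix like that of all lesions. The mix within BI-RADS 5 or any other imaging class is not given, so the size of any overstatement cannot be calculated.

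The conclusion rests on reading the count as bearing on the definite diagnosis named in the aim. It depends on no sample-size or power figure. It is an inexpensive improvement to a secondary outcome and does not affect the primary comparison.

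**What to change.** **Data-analysis.** State which histology classes count as malignant, including where the high-risk lesions named in the LCNB section belong. Replace the two-by-two table by the imaging result against three classes: no malignancy, non-invasive and invasive. Report the PPV for any malignancy and the PPV for invasive carcinoma separately, each with a 95% confidence interval. The NPV can stay as defined.

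**Secondary outcome.** Present the count as women in whom LCNB might be omitted for establishing malignancy only, and show the in-situ/invasive split of the true positives beside it.

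**Cost.** Wording and tabulation only; Table 2 shows that the two carcinoma types are already recorded. The price is smaller cells, wider intervals (most of all in the microcalcification and density subgroups) and a less favourable claim about avoidable biopsies.

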### LCNB

LCNB will be performed under ultrasound guidance or stereotactically. A minimum of four 14 Gauge biopsy specimens per lesion is acquired. The histological diagnosis of the tissue sampled by means of the LCNB provides the definitive diagnosis. Based on histology, patient management will be planned: 'benign lesions' require mammographic follow-up, 'normal breast tissue' requires a repeat LCNB or open breast biopsy and in case of a 'high risk lesion' (i.e. lobular carcinoma in situ, atypical ductal or lobular hyperplasia), 'in-situ carcinoma' or 'invasive carcinoma' require image-guided needle localization followed by surgical excision with appropriate axillary staging (i.e. sentinel node biopsy or axillary lymph node dissection). Patient management will be the same for the MRI and the control group.

If in the intervention group an additional, mammographically occult lesion is detected on the MR images that requires tissue sampling, second-look ultrasound will be performed to determine whether the lesion is ultrasonographically evident and suitable for ultrasound-guided tissue sampling. If the lesion cannot be visualised by means of second-look ultrasound, MRI-guided large core needle biopsy will be performed.

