### Primary outcome

To evaluate whether performing preoperative Breast MRI will improve breast cancer management, we will collect data on all biopsies (including biopsies performed for lesions that were detected on MRI only) and all surgical procedures during 1 year of follow-up after the LCNB. The number of biopsies and surgical procedures in patients in the MRI group will be compared to the number of procedures in the control group.

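### LCNB is both the comparator and the only stated reference in the predictive-value analysis, so its own predictive values cannot be estimated and MRI is charged with LCNB's misses

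*Protocol article*

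**What the plan says.** The purpose of the analysis and its reference standard are both stated under Data-analysis. The purpose is given as: "To compare the diagnostic performance of MRI (in combination with mammography and ultrasound) and LCNB, a two-by-two table will be constructed". In that table the combined imaging results "will be compared to the results of the histology of the tissue sampled at the large core needle biopsy". PPV and NPV are the correctly identified positives and negatives divided by all positive and all negative MRI results.

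The decision statement follows: "If the positive predictive value of mammography, ultrasound and Breast MRI is sufficiently close the positive predictive value of large core needle biopsy", in all patients or in a subgroup, biopsy may be replaced by MRI in future. The section then adds that "whether MRI can indeed replace LCNB in clinical practice will have to be assessed in a separate study".

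The LCNB section supports the choice of reference: "The histological diagnosis of the tissue sampled by means of the LCNB provides the definitive diagnosis". The same section does not treat every LCNB result as final. Normal breast tissue leads to repeat LCNB or open biopsy, high-risk lesions go to excision, and benign lesions are followed by mammography. Under Primary outcome, the trial records all biopsies and "all surgical procedures during 1 year of follow-up after the LCNB".

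**The concern.** A test cannot be compared with its own result. If truth is what LCNB found, LCNB is never wrong and each disagreement is booked as an imaging error. The benchmark in the replacement statement, LCNB's PPV, is then not something the described analysis can estimate, and no outside value is given for it.

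The protocol's own pathway shows where this matters. Take an MRI-positive lesion whose LCNB shows a high-risk lesion or normal tissue, and whose excision or repeat biopsy then shows cancer. Under the stated rule MRI was wrong, although the trial holds histology showing that it was right.

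At stake is the second stated aim: whether a subgroup exists in which imaging with MRI gives a definite diagnosis. The Secondary outcome section uses these predictive values to estimate how many women might avoid LCNB in future.

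**Working it through.** The article gives no margin, power or sample size for this objective, so there is no planned figure to reproduce. The check is a logical one, followed by an illustration of size.

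**Logic.** With LCNB histology as truth, LCNB-positive and truth-positive are the same set, so LCNB's PPV and NPV are both 1. No other reference is named in the analysis.

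**Inputs from the article.** MRI sensitivity 0.90 and specificity 0.72 (Background, meta-analysis). LCNB-malignant share 40/113 = 0.354 (Preliminary results and Table 2; the denominator is samples, 4 of the 109 lesions having been sampled twice).

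**Assumptions.** LCNB sensitivity s between 0.90 and 1.00, LCNB specificity 1.00, LCNB errors independent of MRI errors given true status, and the MRI figures standing in for the imaging combination.

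**Formulas.**
- True prevalence: p = 0.354/s
- True MRI PPV: 0.90p / [0.90p + 0.28(1−p)]
- MRI PPV against LCNB: s × true PPV
- True MRI NPV: 0.72(1−p) / [0.72(1−p) + 0.10p]
- MRI NPV against LCNB: [0.72(1−p) + 0.10p(1−s)] / [0.72(1−p) + 0.10p]
- True LCNB NPV: (1−p) / [(1−p) + (1−s)p]

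Example at s = 0.97: p = 0.365. True PPV = 0.328/(0.328 + 0.178) = 64.9%. Against LCNB it is 0.97 × 64.9% = 62.9%. LCNB NPV = 0.635/(0.635 + 0.011) = 98.3%.

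| Assumed LCNB sensitivity | MRI PPV, true | MRI PPV, against LCNB | MRI NPV, true | MRI NPV, against LCNB | LCNB NPV, true |
|---|---|---|---|---|---|
| 1.00 | 63.8% | 63.8% | 92.9% | 92.9% | 100% |
| 0.97 | 64.9% | 62.9% | 92.6% | 92.8% | 98.3% |
| 0.95 | 65.6% | 62.3% | 92.4% | 92.8% | 97.1% |
| 0.90 | 67.6% | 60.8% | 91.7% | 92.6% | 93.9% |

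The PPV shortfall is 2.0, 3.3 and 6.8 points. The NPV error is under 1 point and runs the other way, because cancers missed by both tests count as MRI true negatives.

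**LCNB's PPV.** At specificity 1.00 it really is 100%. At an assumed specificity of 0.99 it is about 98.2%. The table described could not tell these apart.

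**Subgroups.** Under the same assumptions the PPV against LCNB is s times the true PPV in any subgroup. If a subgroup's true PPV were 96%, the figure the article cites for mammographic BI-RADS 5 lesions, it would appear as 0.97 × 96% = 93.1%, or 0.90 × 96% = 86.4%.

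**The case against.** Four arguments on the other side carry weight.

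- **The plan never says LCNB's PPV will be set at 100%.** A reader might infer this from the table, but the table yields only MRI's predictive values, and the benchmark could be a surgically verified or published figure. This stands. What is shown is that the stated reference cannot supply the benchmark and that no other source is named.
- **The analysis is exploratory.** There is no test or margin, every patient still has LCNB, and replacement is left to a separate study. This stands and limits the consequence, but it does not repair the comparison.
- **Agreement with LCNB has value in itself**, since LCNB directs management. This also stands: MRI's values against LCNB are valid as agreement. They are not predictive values for cancer, and they do not compare the two tests.
- **The bias in PPV is modest and works against MRI.** Under independent errors that is so, and with an overall MRI PPV of about 61% to 68% it would hardly alter the conclusion for all patients. It matters more in high-PPV subgroups, where a few points decide whether two values are close.

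Two figures in the article might seem to make the case stronger and do not. The 5% of patients expected to have DCIS with an occult invasive component would move no cell of a benign/malignant table, because the article counts DCIS as malignant. The 11 of 113 samples that were non-representative or normal tissue (9.7%) show that LCNB is not always conclusive. Nothing says they are scored as true negatives without the repeat sampling that the LCNB section requires.

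**Conclusion.** The point holds, limited to the secondary objective. The Data-analysis section states a reference standard that cannot serve its stated purpose. This is a stated rule with a bad effect, not detail left to another document.

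The size rests on assumptions, since the article gives no LCNB accuracy. For LCNB sensitivity of 0.90 to 0.97, specificity 1.00 and independent errors, MRI's PPV is understated by about 2 to 7 points, and LCNB's NPV is about 94% to 98% where self-comparison would give 100%. Correlated errors or imperfect LCNB specificity would change these figures but not the logic.

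A reader might conclude that the second aim cannot be answered at all. The document does not support that: agreement with LCNB can still be estimated, and the article claims no more than a basis for a separate study. The primary outcome is untouched. The change is worth making, but the trial does not stand or fall by it.

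**What to change.** In Data-analysis, define one final diagnosis per lesion: surgical pathology where the lesion was excised; otherwise repeat-biopsy or LCNB histology, supplemented by the 1-year record of biopsies and surgery and the mammographic follow-up of benign lesions. Score both imaging with MRI and the first LCNB against it in the same lesions. Report PPV and NPV for each, with the difference and its 95% CI. State whether the closeness statement concerns PPV only, as in Data-analysis, or both predictive values, as in the Abstract. Keep the MRI-versus-LCNB table and label it an agreement analysis.

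The cost is low, because the procedures are already performed and recorded for 1 year. There are three drawbacks. The analysis must wait for follow-up. LCNB-benign lesions are verified by follow-up and not by surgery, so verification differs by LCNB result and should be reported as a limitation. The article also does not say that cancer-free status at 1 year is ascertained or when the mammographic follow-up takes place, so what the record can support should be confirmed first.
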